##### Face to Face (FtF) Condition

Participants randomized to the FtF condition will complete the ACT-Adjust intervention in their home, or, if this is not appropriate, at a location accessible for both the participant and the psychologist delivering the intervention.

##### Video-Consulting (VC) Condition

Participants allocated to the video-consulting condition will complete the ACT-Adjust intervention online using the HealthDirect Video Call program (Coviu, 2020) and will be provided with additional equipment to use for the duration of the intervention to facilitate and standardize the telepsychology delivery. Items provided to each participant in this condition include 1 × Samsung Galaxy 10.1 Tablet device and charging equipment with a prepaid data SIM (4G network if available), and one wired headset.

Once randomized to the VC condition, the Research Assistant will schedule a technology home visit with the participant to deliver the Therapy Kit and VC equipment, provide training on using the technology and complete a test run using the VC platform. An appropriate space within the home environment will be established to allow both safety and privacy for the participant while engaging in the intervention. A test of the internet upload and download speeds will also be conducted and recorded by the Research Assistant at the site. The tablet devices have been set up with access restrictions so only the HealthDirect Video Call platform is accessible, with all other icons removed from the home screen to simplify the display. Upon completion of the intervention, and before post-treatment assessment, VC equipment will be collected from the participant by the Research Assistant.

### Treatment Fidelity

To assess treatment adherence, all therapy sessions will be audio recorded by therapists using an app on their mobile phone. These audio files will be uploaded onto the secure servers of South Western Sydney Local Health District (SWSLHD) and then deleted from the therapist's device. The electronic files will be password protected and saved with the unique identifier for each participant. On completion of the study 15% of sessions (pragmatic selection to ensure reviews are completed for all sessions and all therapists) will be reviewed by an independent psychologist skilled in ACT to ensure adherence to the ACT-Adjust protocol. This will involve using both a checklist to ensure the therapist covers all aspects of the ACT-Adjust program and using the Acceptance and Commitment Therapy Fidelity Measure (ACT-FM) (O'Neill et al., 2019). The ACT-FM is a 25-item measure which assesses whether the therapist's behavior is consistent or inconsistent with ACT principles using a four point scale where 0 = “*The behavior never occurred*,” 1 = “*Therapist rarely enacts this behavior*,” 2 = “*Therapist sometimes enacts this behavior*,” and 3 = “*Therapist consistently enacts this behavior*.”

### Measures

Measures will be administered at baseline and for sessional measures, by the psychologist providing the intervention. Post treatment measures will be undertaken by a blinded assessor (see section Blinding for details about the blinded assessor), all assessors will be provided training in administration of the measures by DW to ensure consistency in administration. If required, the measures can be read out to the participant by the assessor to assist with understanding and a separate sheet with the measure's Likert response scales will be provided to the participant in larger font to compensate for vision, attentional/cognitive and reading deficits.

#### Primary Outcome Measures

*Psychological distress*—*Depression Anxiety Stress Scales* −*21 (DASS-21)* (Lovibond and Lovibond, 1995) is a 21-item questionnaire which assesses the constructs of depression, anxiety and stress over a seven-day period. Clinically significant levels of distress on the DASS-21 (87th percentile and above) are defined by the following scores on each subscale; (i) Depression >13, (ii) Anxiety >9, and (iii) Stress >18. The DASS-21 is commonly used in clinical practice within Australia and includes the broader psychological component of stress. The existing factor structure has been replicated in samples with a moderate to severe TBI and internal consistency of the subscales was very good (Cronbach's α > 0.80) (Randall et al., 2017).

*Psychological flexibility*—Acceptance and Action Questionnaire—Acquired Brain Injury (AAQ-ABI) (Whiting et al., 2015) is a nine-item self-report measure scored on a five-point Likert scale with a range of 0–36, with higher scores indicating greater psychological flexibility. Items assess psychological flexibility around the thoughts, feelings and behaviors that may arise after incurring a brain injury, e.g., Item three, “*I stop doing things when I feel scared about my brain injury*.” The measure has sound psychometric properties (e.g., Cronbach's α = 0.89) (Whiting et al., 2015).

#### Secondary Outcome Measures

*Quality of Life—Quality of Life after Brain Injury (QOLIBRI)* (Von Steinbüchel et al., 2010) is a health-related quality-of-life instrument specifically developed for traumatic brain injury (TBI). It has 37 items across six subscales scales; (i) cognition, (ii) self, (iii) daily life and autonomy, (iv) social relationships (v) emotions, and (vi) physical problems. The first four subscales are rated on a five-point Likert scale. It takes around 7–10 min to complete and has robust psychometrics with a Cronbach's α of 0.95 previously reported for the total score (Von Steinbüchel et al., 2010).

*Values identification—Survey of Life Principles (SLP) Version 2.2* is a card sorting task (Ciarrochi, 2009) and will serve a dual role in the study (i) measuring values importance and success; and (ii) during the intervention it is used to assist participants in values identification. The SLP has 60 items reflecting life principles (values) across various domains (e.g., “*acting with courage*,” “*designing things*”). Respondents allocate each principle to one of three categories; (1) not very important; (2) moderate importance; and (3) highest importance. From the highest importance category, respondents select their top 10 and rate them using a five-point Likert scale (0 = “not very” to 4 = “extremely”) on (1) How important was the value (Importance) and (2) How consistently are you acting in accordance with your value (Success). SLP scores of value importance and success have previously demonstrated good internal consistency (Cronbach's α = 0.79–0.97) (Ciarrochi, 2009).

*Committed Action—Engaged Living Scale (ELS)* (Trompetter et al., 2013) is a 16-item self-report measure which assesses an individual's engaged response style as conceptualized in ACT, e.g., Item eight, “*I believe that my values are really reflected in my behavior*.” The ELS uses a five-point Likert scale where 1 = “*completely disagree*” and 5 = “*completely agree*” and a score range (total score) of 16–80. It has been validated in chronic pain research using ACT and provides a better understanding of the mechanisms underlying change in ACT. It has two subscales assessing Valued Living (10 items) and Life Fulfillment (six items) and internal reliability on both subscales and the total scale is good (Valued Living, α = 0.86, Life Fulfillment, α = 0.87, total score ELS, α = 0.90) (Trompetter et al., 2013).

*Satisfaction with Life Scale (SWLS)* (Diener et al., 1985) is a five item, seven-point Likert scale measuring global satisfaction with life and is considered to assess a cognitive component of overall well-being. Higher scores are indicative of greater satisfaction with life. It has been used in several studies with TBI clients with good internal consistency, Cronbach alpha of 0.78 (Kreitzer et al., 2019).

#### Baseline Only Measures

*Repeatable Battery for the Assessment of Neuropsychological Status (RBANS)* (Randolph, 1998) will be used to provide an assessment of cognitive ability and will be administered at baseline only. The RBANS is a brief neurocognitive battery measuring immediate and delayed memory, attention, language, and visuospatial skills and has been found to be suitable for assessing cognitive function after TBI (Randolph, 1998). The RBANS requires approximately 25 min for administration and is broadly used for clinical diagnostic purposes to establish neurocognitive status.

*Project specific demographic questionnaire*—to collect demographic information regarding age, gender, injury circumstances and both premorbid and post injury functioning about work and relationships.

#### Session Measures

##### Pre–session

These measures are used for clinical purposes to assess the participant's emotional functioning on a weekly basis and include the DASS-21 and the AAQ-ABI which are described above.

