### Treatment Conditions

All participants will receive their intervention in conjunction with constrained usual care (Freedland et al., 2011). Usual care may involve prescribed components of multidisciplinary interventions (e.g., social work, physiotherapy, occupational therapy, case management, speech therapy, diversional therapy, and/or vocational assistance) except for clinical psychology, as well as regular medical reviews by a rehabilitation physician and/or general practitioner. Participants who persistently report extremely high levels of psychological distress (DASS-21 subscales in the extremely severe range, as measured at the beginning of each session) or express suicidal intent during therapy, will be removed from the study and offered immediate psychological treatment. In addition, the treating clinician will assess participants' ability to attend to the session material whether from cognitive impairment or fatigue and make necessary treatment adjustments with regard to rest breaks and/or rescheduling sessions.

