Each participant enrolled in the trial will receive a Therapy Kit comprising a hardcopy of the ACT-Adjust 2.0 Client Workbook and individually wrapped materials for Session 2 (Chinese finger trap), Session 5 (packet of sultanas), and Session 6 (values card pack). All participants will complete the ACT-Adjust 2.0 program (Table 1), which is comprised of 9 × 1.5 h sessions. The week prior to commencing the program (and before randomization occurs), participants will meet with the treating psychologist in person to complete Baseline assessments. Sessions 1–7 will occur on a weekly basis, and a 2-week break will be placed between Sessions 7 and 8, and a 4-week break between Sessions 8 and 9. If required, sessions may be rescheduled by arrangement between the participant and treating psychologist, and will be rescheduled as soon after the original session as is feasible. Following the completion of Session 9, participants will meet with an independent blinded assessor to complete the Time 2 assessment measures (within 1 week of treatment completions). Three months after completing Session 9, participants will meet again with an independent blinded assessor to complete Time 3 assessment measures.

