			**Study period**								
			**Enrolment**	**Allocation**	**Post-allocation**						
					**Intervention**				**Evaluation**		
Time Points			T1	T1a	T1b	Weeks 1–7	Week 9	Week 13	T2	T3	T4
					VC training	Session 1–7	Session 8	Session 9			
Enrolment		Eligibility screen	X								
		Informed consent	X								
		Randomization		X							
Interventions		ACT-Adjust FtF									
		ACT-Adjust VC			X						
		Wait list Control									
Assessments	Baseline measures	Demographic data	X								
		RBANS	X								
	Primary Outcome measures	DASS-21	X			X^2^	X^2^	X^2^	X	X	X
		AAQ-ABI	X			X^2^	X^2^	X^2^	X	X	X
	Secondary Outcome measures	QOLIBRI	X						X	X	X
		SLP	X						X	X	X
		ELS	X						X	X	X
		SWLS	X						X	X	X
	Other measures	HTRS^1^				X^2, 3^	X^2, 3^	X^2, 3^			
		SRS V.3				X^3^	X^3^	X^3^			
		VCSE-Client				X^3^	X^3^	X^3^			
		VCSE-Therapist				X^3^	X^3^	X^3^			

1 *Items 1-2 administered at end of the session and Item 3 at the beginning of the following of session*;

2 *Measure administered at the beginning of the treatment session*;

3 *Measure administered at the conclusion of the treatment session. AAQ-ABI, acceptance and action questionnaire-acquired brain injury; DASS-21, depression anxiety stress scales −21; ELS, enhanced living scale; HTRS, home task rating scale; QOLIBRI, quality of life after brain injury; RBANS, repeatable battery for the assessment of neuropsychological status; SWSL, satisfaction with life scale; SRS V.3, session rating scale version 3; VCSE, video consulting session evaluation*.

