### Data Analysis

Data will be entered into SPSS statistics software (IBM Corp, 2019), reviewed for missing data and then screened for normality on all outcome measures and for each treatment group. Prior to the main analysis, between groups comparisons will be undertaken to test for equivalency of the groups using chi-square and *t*-tests. Where participants withdraw or are not contactable for the follow up assessment, the last recorded measures will be carried forward to remaining assessment points for data analysis. Primary analysis will be implemented on an Intention-to-Treat basis, using hierarchical linear mixed models to study the differential effects of each treatment condition. For the post-treatment analyses between the three treatment conditions, analysis will focus on linear time effects, treatment conditions and interactions. Cohen's effect size will be calculated for all analyses. Analyses will focus on the estimated mean differences relative to pre-treatment levels on primary and secondary outcome measures (see Table 3). For the longer-term treatment effects, the non-inferiority of the face-to-face and video consulting will be assessed at the 3-month follow-up.

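### Loss from the ACT arms can follow session DASS-21 scores, but the missing-data rule is carry-forward and leaves the role of those scores open

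*Protocol article*

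**What the plan says.** Four parts of the protocol article bear on this.

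- **Session Measures, Pre-session:** the stated role of the DASS-21 and AAQ-ABI readings taken at each session is "These measures are used for clinical purposes", namely weekly monitoring of the participant's emotional state.
- **Table 3:** both instruments are marked at the sessions of weeks 1–7, 9 and 13, in the primary-outcome rows, with the footnote "Measure administered at the beginning of the treatment session".
- **Treatment Conditions:** participants leave the study on persistent extreme distress, defined by "DASS-21 subscales in the extremely severe range, as measured at the beginning of each session", or if they "express suicidal intent during therapy". They are then offered other psychological treatment.
- **Data Analysis:** for participants who withdraw or cannot be reached, the most recent recorded values fill the remaining assessment points. The primary analysis is by intention to treat, "using hierarchical linear mixed models to study the differential effects of each treatment condition".

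The Wait List Control Condition section gives that group usual care for 13 weeks and then the Time 2 assessment, so it has no session scores before Time 2. Appendix I sets the primary outcome times at baseline, end of therapy and three months.

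**The concern.** One stated route out of the study runs through scores that are observed, and before Time 2 only ACT participants can take it. A likelihood analysis is valid when missingness depends on data in the model. If the model holds only the scheduled assessments, it assumes that Time 1 explains who is missing at Time 2, and the removal rule says otherwise. Distressed ACT participants would drop out of the Time 2 data with no counterpart on the wait list.

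The stated remedy, carry-forward, does not settle this. It fills the gaps before the mixed model is fitted, so the model's own handling of missing data has nothing left to do. For someone removed in mid-therapy it is also unclear which value is carried. At stake is the Time 2 comparison of ACT with the wait list, the only point at which that randomised contrast exists.

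**Working it through.** **Inputs from the article.** Allocation is 16 face-to-face, 16 video and 24 wait list (Randomization), so 32 ACT participants against 24. There are nine sessions before Time 2 (Table 3). The only score that triggers removal is the session DASS-21. No loss rate, SD or within-person correlation is given, so there is no figure of the plan's own to reproduce, and every size below rests on assumptions.

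**Step 1: what is carried.** For a participant removed after session 4, the latest recorded DASS-21 is the session-4 score if session readings count, and the Time 1 score if only scheduled assessments count. Data Analysis fits either reading.

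**Step 2: the form of the bias.** With a fraction *p* of ACT participants missing at Time 2,

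bias in the ACT mean = *p* × (mean value filled in − mean Time 2 score had they stayed).

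Negative favours ACT, because lower DASS-21 is better.

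**Step 3: simulation.** Scores are in SD units: a person effect, a week-to-week autoregressive part (0.9) and measurement error (variance 0.2). Removal follows two or three consecutive session scores above a cut-off. This stands in for the removal rule and is not a reading of it. The same score is both trigger and outcome. Selected results, with bias divided by *p* in brackets:

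| Person variance; courses | True effect | Rule | *p* | Scheduled assessments only | Carry session score | Carry Time 1 | Model with session scores |
|---|---|---|---|---|---|---|---|
| 0.3; parallel | 0.5 | 2 above 1.0 | 0.176 | −0.104 (−0.59) | +0.211 (+1.20) | +0.125 (+0.71) | 0.000 |
| 0.3; parallel | 0 | 3 above 1.0 | 0.143 | −0.091 (−0.64) | +0.103 (+0.72) | +0.024 (+0.17) | 0.000 |
| 0.5; diverging | 0 | 2 above 1.0 | 0.242 | −0.253 (−1.05) | +0.097 (+0.40) | −0.054 (−0.22) | 0.000 |
| 0.5; diverging | 0.5 | 2 above 1.0 | 0.185 | −0.177 (−0.96) | +0.147 (+0.79) | +0.063 (+0.34) | 0.000 |
| 0.5; diverging | 0.5 | 2 above 2.0 | 0.024 | −0.027 | +0.022 | +0.005 | 0.000 |

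A carried session score was selected for being high, so it overstates later distress. A carried Time 1 score gives removed participants no improvement, so its bias moves with the true effect: −0.054 becomes +0.063 in the two otherwise equal rows.

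**Step 4: trial size.** At 32 v 24 with 9–23% removed, separate runs gave these biases:

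- Time 1 only: −0.04 to −0.14 SD
- carrying the last session score: +0.10 to +0.18 SD
- carrying Time 1: +0.01 to +0.12 SD
- Time 1 plus the last two session scores, pooled over the ACT arms: −0.04 to about 0 SD, with an SD of the estimate 2–5% larger than with Time 1 only

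With no true effect and about 22% removed, the Time 1-only estimate averaged −0.12 SD against a standard error of 0.24. It was significant in favour of ACT in 6.6% of trials (nominal 2.5%). At about 9% removed the figures were −0.05 SD and 4.1%.

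**Step 5: where this stops holding.**

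- Random dropout: 0.00 SD.
- Improvers leaving (20% missing): +0.06 SD, against ACT.
- Missingness driven by the Time 2 state itself: session scores only reduce the bias, from −0.14 to −0.11 SD.
- Effect including what follows removal: if the removed 16.7% change by 0.3 to 0.6 SD afterwards, the session-score model is off by 0.167 × 0.3 = 0.05 to 0.167 × 0.6 = 0.10 SD, in either direction.

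**The case against.** The strongest objection is that a condensed article need not list auxiliary variables, and an analysis plan that is not shown may do so. That would answer a point resting on silence. Here the article fixes a method, carry-forward, and that method is biased under the article's own removal rule on either reading of the value carried.

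Three stronger readings are tempting, and the text does not support them.

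- A reader might infer that session scores are barred from the analysis. The Pre-session section states a clinical purpose but does not say it is the sole one. Table 3 puts the scores in the primary-outcome rows, and the carry-forward sentence could include them.
- A reader might infer that the plan as it stands favours ACT. That direction belongs to a mixed model on the scheduled assessments without carry-forward, which the article does not plan. A carried session score works against ACT, and a carried Time 1 score can go either way.
- A reader might infer that both instruments drive removal. Only the DASS-21 does, beside suicidal intent. The simulated sizes therefore apply to the DASS-21; for the AAQ-ABI they were not worked out.

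It is also fair to say that the bias is modest beside the standard error: 0.12 against 0.24 at heavy loss, and only about 0.01 to 0.05 SD at 1–4% removed. That limits the urgency but does not justify keeping the rule.

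**Conclusion.** The point holds in a limited form. Loss from the ACT arms before Time 2 can depend on observed session DASS-21 scores, and the wait list has no such route. The stated carry-forward rule handles this badly and does not say which value it carries. Moving to a mixed model on Time 1 to Time 3 alone would favour ACT by about 0.04 to 0.14 SD at 9–23% removed; wider assumptions, with diverging courses and 24% removed, reach 0.25 SD. Loss rates, correlations and cut-offs are all assumed.

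The direction is firm only for loss that follows session distress. In video versus face-to-face the bias largely cancels if loss is similar in both modes. Session scores correct the estimate only for the outcome had participants stayed in ACT, and only where the scores explain the missingness. It would be wrong to conclude that they remove all bias from an intention-to-treat effect that includes treatment after removal. The removal rule itself is not judged here.

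**What to change.** In Data Analysis, replace carry-forward with a mixed model or multiple imputation, and state the following.

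- Time 1, Time 2 and Time 3 remain the only endpoints. Session scores serve only to inform missing values.
- For ACT participants missing Time 2 or Time 3, the model includes Time 1 and a small summary of the pre-session scores of the same measure, such as the mean of the last two attended. When the AAQ-ABI is imputed, the session DASS-21 is added.
- The model is fitted across both ACT arms with a term for delivery mode. Using every session score within each arm is not workable: nine sessions × two measures = 18 predictors for 16 participants.
- The result estimates the outcome had participants stayed in ACT. A sensitivity analysis varies the course after removal.

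Align the Pre-session paragraph by adding this use of the scores. The cost is entry of scores already collected, one imputation model and a standard error a few percent larger.

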##### Post-session–Clinical

*Session Rating Scale V. 3.0 (SRS)* (Duncan et al., 2003)—to assess therapeutic alliance between the participant and the therapist (both active treatment arms). The SRS is a short four-item measure to rate the experience of the treatment session from the perspective of the client. It covers the therapeutic relationship, goals and topics, the approach of the therapist and an overall session rating.

*Home Task Rating Sheet*—A measure of homework completion and adherence developed in the original ACT-Adjust study (Whiting et al., 2020). After the home task has been discussed with the participant, they are asked to rate how confident and how motivated they are to complete the home task using a five-point Likert scale of 1 = “Not at all” to 5 = “Totally.” At the beginning of the following session, after home tasks have been reviewed and discussed, participants are asked to rate their satisfaction with their home task completion on the same five-point scale. Any barriers to completing the task are selected from a tick list, e.g., “forgot,” “too busy,” discussed and any alternative reasons for non-completion of home tasks are noted by the therapist.

